#### Exclusion criteria

Individuals with dentofacial anomalies or incomplete permanent dentition to the second molar, or who are currently undergoing orthodontic or orthopedic treatment of the jaws, or who are undergoing psychological treatment or physical therapy and make use of a muscle relaxant, anti-inflammatory agent, or bite plate will be excluded from the study.

### Procedures

As the proposed study constitutes a randomized clinical trial, the recommendations of the Consolidated Standards of Reporting Trials (CONSORT) [26] will be followed to allow greater transparency and enhance the quality of the findings. The subjects will be allocated to five groups, as delineated in Table 1.

**Table 1 T1:** Summary of experimental conditions

**Group**	**TMD**	**Laser application site**	**Therapeutic intervention**
I	Absent	—	Control group
II	Present	TMJ	LLLT
III	Present	Muscles of mastication	LLLT
IV	Present	TMJ and muscles of mastication	LLLT
V	Present	TMJ and muscles of mastication	Placebo

#### Diagnosis of temporomandibular disorder

Prior to any intervention, participants eligible for the study will be diagnosed with TMD, using the Research Diagnostic Criteria for Temporomandibular Disorders (RDC/TMD) questionnaire. Moreover, a specific clinical examination will be carried out by a single, previously trained, examiner. This examination will consist of palpation of the temporal, masseter, digastric and medial pterygoid muscles, palpation of the TMJs and an analysis of the mandible with the aid of a digital caliper to measure vertical and horizontal movements and a stethoscope to assess joint noises. The following will also be investigated: frequent headache, facial pain, fatigue, and difficulty during mastication, bruxism (clenching or grinding of teeth), psychological status, and parafunctional habits.

#### Surface electromyography

The EMG signal will be determined using a four-channel acquisition system (*EMG System do Brasil Ltda*) made up of a signal conditioning module, active bipolar electrodes with 20× pre-amplification, analog band-pass filter (20 to 500 Hz) and 120 dB common rejection mode. The sampling frequency will be 2 kHz. The signal will be digitized using an analog-to-digital converter with 16-bit resolution. The acquisition program will be EMGLab (*EMG System do Brasil Ltda*).

To capture the EMG of the right and left masseter and anterior temporal muscles, the skin will be cleaned with alcohol to diminish impedance and disposable, self-adhesive anterior surface electrodes (Ag/AgCl, Meditrace) measuring 10 mm in diameter will be attached to the belly of the muscle in the region with the greatest tone after the volunteer performs moderate intercuspation. The interelectrode distance will be 20 mm from center to center, as suggested by the European Recommendations for Surface Electromyography [27]. An electrode placed on the left wrist of the volunteer will be used as reference to impede the interference of external noise.

The EMG activity of the masseter and anterior temporal muscles will be read under three conditions: (i) at rest; (ii) during chewing (isotonic); and (iii) during maximum intercuspation (MI) (isometric). The signals referring to the resting and chewing conditions will be measured with no material placed between the upper and lower arches. During the readings, the volunteer will remain seated comfortably in a chair with hands resting on the thighs. Three readings will be made under each condition, with a three-minute rest interval between readings. The readings in the resting position will be taken first and each reading will last 15 seconds. The readings for the chewing condition will be taken next, with the volunteer simulating habitual chewing at a pace determined by a metronome adjusted to 60 beats a minute; each reading will last 15 seconds. The MI readings will then be performed. Three 10-second readings will be performed with no material placed between the arches, followed by three 5-second readings during maximum clenching effort (MCE) with a folded layer of Parafilm M® [28], 3 mm thick (15 mm × 35 mm) between the molars (bilaterally).

The EMG will be carried out before and after LLLT treatment.

### EMG signal processing

To determine EMG activity in the masseter and temporal muscles at rest and during MCE, the signal will be rectified by a mobile mean of 200 ms based on the root mean square (RMS) of the amplitude of the signal. For each condition, a 4-second range will be selected in which the RMS is the most constant. The mean RMS in this time interval (RMS_raw_) will be normalized by the RMS obtained during MCE (RMS_MCE_). The values referring to the resting and MI conditions will be expressed as a percentage of RMS_MCE_:

$$\%\mathrm{RMS}=\left({\mathrm{RMS}}_{\mathrm{raw}}/{\mathrm{RMS}}_{\mathrm{MCE}}\right)\times 100.$$

The EMG signal during chewing will be rectified and normalized using the peak of the signal followed by the calculation of the RMS. Signal processing will be performed using specific routines of the Matlab program, version 7.1 (MathWorks Inc., Natick, MA, USA).

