## Background

Temporomandibular disorder (TMD) is a term used for a large number of clinical signs and symptoms that affect the muscles of mastication, the temporomandibular joint (TMJ) and associated structures [1-9]. Postural and occlusal abnormalities, parafunctional habits, and psychological factors can lead to TMD [2,4,5,8]. Orofacial pain is the most common complaint among individuals with this condition [2,4,5]. Other symptoms include sensitivity in the muscles of the head and neck region (including the muscles of mastication), pain in one or both TMJs, limited mandibular movements, joint noises, [1-7,10-14] headache, [1-6,10] dizziness, hearing loss and ringing in the ears [2-5]. The presence of symptoms can affect the quality of life and the social life of the patient.

The stomatognathic system includes the maxilla, mandible, teeth, TMJs, and muscles of mastication and is directly related to the cervical spine. The neuromuscular influences of the neck region and the function of mastication actively participate in mandibular movements and the positioning of the cervical spine. Balance and synchrony between the anterior and posterior muscles of the head and neck are needed to establish the resting position of the mandible [4,5].

Alterations in postural balance result in a change in electrical activity in the muscles of mastication, which can be determined using electromyography (EMG) [4]. Electromyographic analysis of these muscles can provide information regarding physiological abnormalities in the stomatognathic system of individuals with TMD in an effort to clarify the relationship between electrical activity and the mechanical response of the muscles [15,16].

Occlusal interferences are related to signs and symptoms of TMD [17,18], can affect chewing function and can lead to asymmetry in the stomatognathic system. Studies involving individuals with adequate occlusion (absence of dysfunction) have demonstrated that mastication occurs with symmetrical activity between the right and left masseter and temporal muscles. However, the muscle contraction pattern is altered and asymmetrical in individuals with occlusal interferences, as demonstrated by EMG during mastication [17].

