#### Application of low-level laser therapy

A gallium-aluminum-arsenide laser (Twin Flex Evolution®, MM Optics) will be employed for the LLLT and placebo treatment. The sessions will be held in a reserved, noise-free room. The volunteer will be positioned with the Frankfurt plane parallel to the ground. The active tip of the laser will be covered in disposable plastic wrap to avoid cross-contamination and for hygiene reasons. The operator will wear suitable protective clothing. The skin at the site to be irradiated will have previously been cleaned with 70% alcohol. Both the operator and volunteer will use protective eyewear.

Two sessions of LLLT or placebo treatment will be carried out over six weeks (a total of 12 sessions). The device will be calibrated with a wavelength of 780 nm, an energy density of 25 J/cm^2^, a power of 50 mW, and a power density of 1.25 W/cm^2^. The exposure time will be 20 s per point, resulting in a total energy of 1 J per point. The spot application method will be used: the laser will have a conventional tip in contact with the skin and will cover an area of 0.04 cm^2^, as suggested by Venezian *et al*. [24] and Carvalho *et al*. [14]. Three of the four groups with TMD will receive LLLT and one will receive a placebo treatment:

1. TMJ region: five points around the TMJ [7,13], totaling 5 J.

2. Masseter and temporal muscles: three points on the masseter (upper, middle and lower) and one point on the anterior temporal [24], totaling 4 J.

3. Mixed application: TMJ and muscles of mastication [12,14], resulting in 9 J.

4. Placebo treatment: the same equipment will be used with a pen that emits a red guide light and a warning sound, but without the emission of a laser beam.

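### Chewing EMG divided by the peak of its own signal cannot register a proportional change in muscle activity

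*Protocol article*

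**What the plan says.** Under Surface electromyography, the masseter and anterior temporal muscles are read in three conditions: rest, simulated chewing and MI. A maximum clench on Parafilm (MCE) closes the sequence. On timing, the section says: "The EMG will be carried out before and after LLLT treatment".

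Under EMG signal processing, the conditions are scaled in two different ways:

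- Rest and MI: "The values referring to the resting and MI conditions will be expressed as a percentage of RMS_MCE", that is, the raw RMS divided by the RMS at MCE, times 100.
- Chewing: "The EMG signal during chewing will be rectified and normalized using the peak of the signal followed by the calculation of the RMS".

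The text does not say which peak is meant for chewing, or which session's MCE is the denominator for rest and MI. The aim at the end of the Background is the effect of laser therapy on EMG activity in these muscles. The statistical section compares mean EMG signals before and after treatment and between groups.

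**The concern.** A ratio whose numerator and denominator come from the same recording loses its scale. If treatment makes the muscle work at a lower or higher level throughout the chewing cycle, the RMS and the peak move together and the ratio stays put.

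Level is a natural target here. The aim refers to EMG activity, and the Discussion links TMD pain to increased muscle activity. A chewing comparison showing no difference could then be reported as no effect of laser therapy on chewing activity, when the index could not have shown a proportional effect. Both the before-after and the between-group comparisons of this condition would be affected. Because the processing rule is stated outright, this is a choice the document makes, not a detail it leaves for later.

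**Working it through.** The protocol gives no numerical result for the chewing index, so there is no figure to reproduce. The check is algebra, confirmed on a simulated signal.

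**Step 1. The index.** For a recording x, rectifying, dividing by the peak and taking the RMS gives

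I(x) = RMS(|x| / max|x|) = RMS(x) / max|x|.

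**Step 2. Scale the signal.** If treatment multiplies the whole signal by k > 0,

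I(kx) = k·RMS(x) / (k·max|x|) = I(x).

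The change is zero for k = 0.7 (a 30% fall), k = 0.5 (a 50% fall) and every other k. Using one common peak for all chewing readings of a session gives the same result, because that peak is also multiplied by k.

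**Step 3. Numerical confirmation.** From the protocol: 15-second readings, 2 kHz sampling, chewing paced at 60 per minute. Assumed: Gaussian noise under a once-per-second burst envelope with a small between-burst floor of 0.05.

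| Scale k | Raw RMS | Peak-normalised RMS |
|---|---|---|
| 1.0 | 0.456 | 0.1114 |
| 0.9 | 0.411 | 0.1114 |
| 0.8 | 0.365 | 0.1114 |
| 0.7 | 0.319 | 0.1114 |
| 0.5 | 0.228 | 0.1114 |
| 1.3 | 0.593 | 0.1114 |

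**Step 4. What the index can still see.** Changing the between-burst floor alters the signal non-proportionally. With a fresh noise draw each time, floors of 0.02, 0.05, 0.1 and 0.2 gave 0.1140, 0.1079, 0.1251 and 0.1284. So the index responds to pattern. It is also noisy, because the peak is a single sample: the same floor of 0.05 gave 0.1114 in one draw and 0.1079 in another, about 3% apart (0.0035 / 0.1114).

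**Step 5. The alternative denominator.** With %RMS = 100 × RMS_chewing / RMS_MCE, a chewing factor a and an MCE factor m change the outcome by a/m − 1.

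- MCE unchanged (m = 1), chewing down 20% (a = 0.8): −20%, so the level change is visible.
- Chewing unchanged (a = 1), MCE up 10%, up 25% or down 20% (assumed range): −9.1%, −20% or +25%.
- Both down 20%: 0.8/0.8 − 1 = 0%.

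The new ratio registers level, but relative to the clench. RMS_MCE therefore has to be shown beside it.

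**The case against.** **The aim names no component of EMG activity.** It does not specify absolute chewing amplitude, and an index of pattern is a legitimate measurement. This stands in part. The protocol may want a pattern measure, but it does not say so, and a reader would take an effect on EMG activity to include its level.

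**Normalisation is needed.** Disposable electrodes "will be attached to the belly of the muscle in the region with the greatest tone after the volunteer performs moderate intercuspation", so raw amplitude can differ between sessions for reasons unrelated to treatment. This stands, and it is why the remedy keeps a reference contraction and does not move to raw RMS alone.

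**Dividing by the clench brings in a denominator that treatment might change.** The muscle-treated groups receive laser at "three points on the masseter (upper, middle and lower) and one point on the anterior temporal", and these muscles produce the clench. This also stands. It is the price of the remedy and the reason to report RMS_MCE by group.

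Four stronger readings are tempting, and the document does not support them:

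- *Every change in amplitude is cancelled.* Only proportional changes are; Step 4 shows that others move the index.
- *The trial loses the right-left asymmetry it is looking for.* The Background remark that "the muscle contraction pattern is altered and asymmetrical in individuals with occlusal interferences, as demonstrated by EMG during mastication" describes other people's findings. No asymmetry index or right-left comparison is planned.
- *The rest and MI outcomes are invalid because treatment may alter the clench.* Nothing in the document shows that it does. The percentage of MCE is openly defined, and its randomised comparison is a valid effect on relative activity.
- *The sample-size means of 13.4 and 11.9 show how large a clench change would mimic the planned effect.* That section gives neither the unit nor the EMG condition, so no such figure can be drawn from it.

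**Conclusion.** The point holds for the chewing condition. As written, the chewing index is exactly blind to a proportional change in activity: a uniform 30% or 50% fall gives 0% change. It measures burst pattern relative to peak and stays sensitive to non-proportional changes.

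The conclusion rests on one assumption, that the peak is taken from the chewing recording itself (or from the same session's chewing readings). If the sponsor meant a peak from another source, the algebra no longer applies in this form, but the sentence must then be corrected to name that source.

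The reach is limited to one of three EMG conditions. For rest and MI, the only request is to state which session's MCE is the denominator and to show RMS_MCE so that the ratio can be interpreted. The change should be made before analysis, and it does not call the trial's design into question.

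**What to change.** 1. Make the main chewing outcome the RMS of the un-normalised chewing signal as a percentage of the same-session RMS_MCE, the reference already used for rest and MI.
2. Keep the peak-normalised value as a secondary descriptor of burst shape, and state whose peak is used.
3. State that the same-session MCE is the denominator in all three conditions.
4. Report RMS_MCE by randomised group before and after treatment, so that a change in %RMS at rest, in MI or in chewing that is driven by the clench can be seen.

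**Cost.** The MCE readings are already scheduled, so this needs an edit to the Matlab routine and a few extra table rows. The article reports the trial as still recruiting, and if raw signals are kept nothing has to be measured again.

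**Downsides.** The chewing outcome will depend on a voluntary maximum clench that treatment might change. The accompanying RMS_MCE figures will be noisier than the ratios, because electrodes are placed anew at each session.

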#### Evaluation of occlusal contacts

The type of occlusion will be determined by the clinical examination based on the Angle classification [29], which is the most practical classification and is considered the gold standard in the literature. This system is based on anteroposterior relationships between the arches:

•Angle Class I (neutral occlusion): the mesiovestibular cusp of the permanent upper first molar articulates with the buccal sulcus of the permanent lower first molar.

•Angle Class II (distal occlusion): the mesial sulcus of the permanent lower first molar articulates posteriorly to the mesiobuccal cusp of the permanent upper first molar.

•Angle Class III (mesial occlusion): the mesial sulcus of the permanent lower first molar articulates anteriorly to the mesiobuccal cusp of the permanent upper first molar.

The T-Scan® III system will be used to record occlusal contact points. This system is composed of contact sensors connected to a USB port of a computer. Occlusal forces are recorded using a specific software program. The volunteer will be positioned in a chair at 90 degrees such that the Camper plane is parallel to the ground and will be instructed to perform MI. The T-Scan® III allows the simultaneous recording and imaging of the distribution of occlusal forces and time sequences, as well as premature contacts and interferences in the occlusion dynamics [30].

Determination of occlusal contact points will be made at the beginning and end of treatment as well as 30 days after the last session.

#### Evaluation of mandibular range of motion

The guidelines of the International Association for Dental Research will be followed when evaluating the range of motion of the mandible; the guidelines recommend a single measurement of each movement [31]. The volunteer will be instructed to open the mouth as wide as possible. Maximum voluntary mouth opening (distance between upper and lower central incisors) will be recorded with the aid of a digital caliper. The volunteer will then be instructed to exert pressure on the lower teeth with the index and middle finger to obtain maximum passive mouth opening and move the mandible to the right and left for the determination of excursion (distance between upper and lower midpoints). These procedures will be carried out at the beginning and end of treatment as well as 30 days after the last session [1,2].

#### Evaluation of pain

A visual analog scale will be used before and after LLLT as well as 30 days after the last session to record pain upon palpation of the masseter and temporal muscles [1,2,9,24]. This is a numeric rating scale that runs from 0 (absence of pain) to 10 (worst pain imaginable) [1].

#### Application of low-level laser therapy

A gallium-aluminum-arsenide laser (Twin Flex Evolution®, MM Optics) will be employed for the LLLT and placebo treatment. The sessions will be held in a reserved, noise-free room. The volunteer will be positioned with the Frankfurt plane parallel to the ground. The active tip of the laser will be covered in disposable plastic wrap to avoid cross-contamination and for hygiene reasons. The operator will wear suitable protective clothing. The skin at the site to be irradiated will have previously been cleaned with 70% alcohol. Both the operator and volunteer will use protective eyewear.

Two sessions of LLLT or placebo treatment will be carried out over six weeks (a total of 12 sessions). The device will be calibrated with a wavelength of 780 nm, an energy density of 25 J/cm^2^, a power of 50 mW, and a power density of 1.25 W/cm^2^. The exposure time will be 20 s per point, resulting in a total energy of 1 J per point. The spot application method will be used: the laser will have a conventional tip in contact with the skin and will cover an area of 0.04 cm^2^, as suggested by Venezian *et al*. [24] and Carvalho *et al*. [14]. Three of the four groups with TMD will receive LLLT and one will receive a placebo treatment:

1. TMJ region: five points around the TMJ [7,13], totaling 5 J.

2. Masseter and temporal muscles: three points on the masseter (upper, middle and lower) and one point on the anterior temporal [24], totaling 4 J.

3. Mixed application: TMJ and muscles of mastication [12,14], resulting in 9 J.

4. Placebo treatment: the same equipment will be used with a pen that emits a red guide light and a warning sound, but without the emission of a laser beam.

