## Methods/Design

A randomized, controlled, double-blind, clinical trial will be carried out. The protocol for this study received approval from the Human Research Ethics Committee of the *Universidade Nove de Julho* (São Paulo, Brazil) under process number 40455. The legal guardians of the participants will sign a statement of informed consent authorizing participation in the study. Figure 1 summarizes the trial design.

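### Placebo is given only in the two-site pattern, so double-blinding cannot be ensured for the TMJ-only and muscle-only laser groups against placebo

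*Protocol article*

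**What the plan says.** The opening of Methods/Design states: "A randomized, controlled, double-blind, clinical trial will be carried out". The abstract says the same. Neither place says which parties are blinded.

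Table 1 (Procedures) gives each TMD group a laser application site and an intervention:

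- Group II: "Present TMJ LLLT"
- Group III: "Present Muscles of mastication LLLT"
- Group IV: "TMJ and muscles of mastication LLLT"
- Group V: "TMJ and muscles of mastication Placebo"

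Group I has no TMD and receives no application.

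The section on application of low-level laser therapy gives the point counts. The TMJ treatment uses "five points around the TMJ" (5 J), the muscle treatment uses three masseter points and one anterior temporal point (4 J), and the mixed treatment delivers 9 J. For placebo, "the same equipment will be used with a pen that emits a red guide light and a warning sound", but no beam is emitted. That section gives no point count for placebo and mentions no inactive application at the untreated site in Groups II and III.

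**The concern.** A sham pen that looks and sounds like the active one masks the beam. It cannot mask the location of contact. If location differs between groups and only one location pattern ever contains placebo, then location carries information about allocation.

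Two things are at stake in II versus V and III versus V. The first is knowledge of treatment. The operator meets the participant at all 12 sessions and, in a one-site session, knows from the pattern that the laser is active. The second is the comparison itself. These contrasts differ in where the pen touches and probably for how long, as well as in laser on or off. Pain is rated by the participant on palpation of the masseter and temporal muscles (Evaluation of pain). Group V has sham contact at those muscles, whereas none is described for Group II. A difference in pain between II and V could therefore reflect contact and attention at the rated site as well as the laser. Maximum mouth opening, and the maximal clench used to normalise the EMG, also depend on effort.

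**Working it through.** The plan states no figure to reproduce here. The check is a cross-tabulation of application pattern against treatment, followed by the contact times.

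**Inputs.** Sites and interventions for Groups II to V come from Table 1. Group size is 17 (Sample size calculation). Point counts and 20 s per point come from the laser section. Consistency check: 5 × 17 = 85, the total in the abstract. The four TMD groups contain 4 × 17 = 68.

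**Step 1. Share on active laser, given the pattern.** Formula: active participants with the pattern ÷ all participants with the pattern.

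| Pattern | Groups | Active | Total | Share active |
|---|---|---|---|---|
| TMJ only | II | 17 | 17 | 1.00 |
| Muscles only | III | 17 | 17 | 1.00 |
| Both sites | IV, V | 17 | 34 | 0.50 |

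Participants whose pattern allows active treatment to be deduced: 17 + 17 = 34, and 34/68 = 50%. This is an upper bound on unmasking, because the deduction requires knowing both the pattern and the arm structure.

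**Step 2. Matched contrasts.**

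- II versus V: TMJ against both sites, not matched.
- III versus V: muscles against both sites, not matched.
- IV versus V: both sites in each group, matched.

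So one of the three laser-versus-placebo contrasts isolates laser on or off.

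**Step 3. Contact time for one set of points.** Formula: points × 20 s.

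- II: 5 × 20 = 100 s
- III: 4 × 20 = 80 s
- IV: 9 × 20 = 180 s (9 J at 1 J per point gives nine points)
- V: 180 s, on the assumption that placebo follows the same nine points as IV

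These are times per session only if one set of points is applied each time. The article does not say whether the counts are per side. If both sides are treated with a full set, the times double to 200, 160 and 360 s. The ratios to V stay the same: 100/180 = 0.56 for II and 80/180 = 0.44 for III.

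Steps 1 and 2 need only the sites in Table 1 and the group size. They do not depend on the placebo point count.

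**The case against.** The strongest reply is that double-blind may refer to the participant and the outcome examiner, and that pattern alone need not unmask either. A participant sees only his or her own treatment, and nothing says that participants are told placebo is always two-site. The article mentions a trained examiner and an operator without saying whether they are the same person, so the examiner may never see a session. This stands. A reader might infer from Table 1 that blinding has failed outright, or that 34 participants will know they are on laser. The article supports neither. It shows that the operator can tell, that anyone else who knows the arms can tell, and that no described safeguard prevents it.

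A second reply is that an article condenses a fuller protocol, which might specify inactive contact at the untreated site. That cannot be excluded. But Table 1 lists an application site for the placebo group too, so its site column most naturally means where the pen is applied, whether or not it is active. On that reading the mismatch is a stated design feature and not an omitted detail.

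A third reply is that the sample size rests on masseter EMG, and the between-group t test and analysis of variance are named for EMG and occlusal contacts, which instruments record. This lowers the risk for those outcomes but does not remove it, because clenching depends on effort. Pain is also among the stated aims.

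Finally, a reader might infer that the laser benefit will be inflated. That does not follow. Awareness of active treatment could favour laser, while the extra contact in Group V could favour placebo.

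**Conclusion.** The point holds as a limit on what the design can ensure. As written, the stated double-blinding cannot be guaranteed for II versus V or III versus V, and those two contrasts mix the laser effect with differences in contact site and probably contact time. IV versus V is pattern-matched and is not affected.

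Up to 34 of the 68 TMD participants have a pattern that implies active laser. The contact times of 100 s and 80 s against 180 s rest on two assumptions: nine placebo points, and one set of points per session. The point also assumes that Groups II and III receive no undescribed sham contact. Concern is greatest for self-rated pain and less for EMG and T-Scan recordings. The direction and size of any bias cannot be derived from the article. No later analysis can supply the missing one-site control, so the matter should be settled before treatment rather than at reporting.

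**What to change.** Apply the inactive pen (guide light and sound, no beam) at the muscle points in Group II and at the TMJ points in Group III. Leave the active exposure in every group as it is. All four TMD groups then have the same contact pattern from the participant's side, and Group V becomes a matched control for all three laser groups. State explicitly that Group V receives sham at the same nine points.

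This masks participants but not the operator, who would hold an active pen at one site and an inactive pen at the other, unless the pens are coded by someone else. So also keep the outcome examiner away from the treatment sessions, and state who is blinded and by what means.

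The cost is protocol wording plus extra sham contact per session: 4 × 20 = 80 s in Group II and 5 × 20 = 100 s in Group III, or twice that if both sides receive a full set. The sham equipment is already in the plan. Trial status describes a trial still recruiting and diagnosing, so the change may still be possible. Coding the pens would add a small preparation task.

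If the sham contact is not added, limit the double-blind claim to IV versus V, and report II versus V and III versus V as contrasts without matched application patterns.
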